## Abstract

**Background:**

Many children do not meet current UK physical activity (PA) guidelines. Girls are less active than boys throughout childhood, and the age-related decline in PA, particularly from early adolescence, is steeper for girls than for boys. Dance is the favourite form of PA among UK secondary school aged girls. Delivering dance sessions after school could make a significant contribution to girls’ PA. Therefore, after-school dance sessions may be an appropriate and cost-effective activity through which adolescent girls’ PA levels can be increased.

**Design:**

Two-arm cluster randomised control trial and economic evaluation conducted in 18 secondary schools across the greater Bristol area. All Year 7 girls in participating schools will receive a 'taster’ dance session and subsequently be invited to participate in the project. There is space for up to 33 girls to participate in each school. Schools will be randomly assigned in equal numbers to intervention or control arms after baseline data has been collected. The nine intervention schools will receive a 20 week after-school dance-based intervention, consisting of 40 × 75 minute sessions, delivered by external dance instructors. Control schools will not receive the dance intervention. All measures will be assessed at baseline (time 0), at the end of the intervention period (time 1) and six months after the intervention has ended (time 2). Our primary interest is to determine the effectiveness and cost-effectiveness of the intervention to affect the objectively-assessed (accelerometer) mean weekday minutes of moderate-to-vigorous PA (MVPA) accumulated by Year 7 girls one year after the baseline measurement (time 2).

**Discussion:**

This paper describes the protocol for the Bristol Girls Dance Project cluster randomized controlled trial and economic evaluation, which is attempting to increase MVPA among Year 7 girls in UK secondary schools.

**Trial registration:**

ISRCTN52882523.

## Background

Physical activity (PA) is associated with lower levels of a number of health-based risk factors including insulin, glucose, blood pressure, body mass and is also associated with improved emotional well-being and self-esteem among young people [1]. Despite the benefits of regular PA, many young people do not meet the current UK recommendation of an hour of PA on most days of the week [2]. PA levels decline during childhood, with the start of secondary school a key period of change [3]. Girls are less active than boys throughout childhood and the age-related decline in PA, particularly from early adolescence, is steeper for girls than boys [3].

Organised after-school PA programmes that focus on increasing PA opportunities for a wide group of adolescents could be an effective means of engaging inactive adolescents in PA [4]. A systematic review reported that there had been five evaluations of after-school PA interventions that had employed objective evaluation methods [5]. Of the five studies, three interventions reported positive effects on PA while a fourth pilot study reported a trend towards increased PA when compared to the control group. Four of the five interventions were well received by the children and their parents. With the exception of one study conducted in Spain [6], all studies were conducted in the USA. Thus, although many UK secondary schools offer organised after-school PA programmes, a rigorous and systematic evaluation of this type of intervention has not been conducted.

Interventions that have been based on psychological theory have been more successful than those that have not, and psychological theories can provide key advances for intervention design as they facilitate the identification of key mediators and mechanisms of behaviour change [7]. Self-determination theory (SDT) [8] may be particularly appropriate for understanding adolescents’ PA [9] because it focusses on understanding the quality of individuals’ motivation (e.g. how self-determined their reasons for PA are). SDT contends that finding ways in which adolescents can develop a sense of choice and ownership over their own PA (autonomy), feel competent engaging in PA (competence), and feel supported within a broader social context (relatedness) will foster more self-determined forms of motivation (e.g. participating for fun or personally valued benefits) which are in turn positively associated with PA [8,10]. SDT therefore suggests that PA interventions which target enjoyable and valued activities and foster perceptions of ownership, competence and belonging, are more likely to result in a sustained behaviour change.

Dance is the favourite form of PA among UK adolescent girls [11] and is a desirable activity in which they can engage [12]. Dance overcomes many barriers to adolescent girls’ participation in PA as it is usually group-based (less likely to lead to public display and offers social interaction), non-competitive, and usually takes place indoors (not affected by weather). Dance therefore provides an appropriate medium through which to increase girls’ PA and apply SDT as it is has the potential to be intrinsically motivating and build girls’ perceived autonomy, competence and relatedness. Many girls who would normally drop out of other forms of PA during secondary school will engage in dance when it is available [13].

The applicability of a UK dance-based intervention to increase PA has not been tested. Delivering dance sessions after school, and focussing on increasing girls’ desire to engage in dance and their ability to take part with or without adult instruction, could make a significant contribution to girls’ PA levels.

### Feasibility trial

The Bristol Girls Dance Project (BGDP) feasibility study [14] was a three-arm, parallel group, cluster randomized controlled pilot trial and economic evaluation, with schools as the unit of allocation. Seven secondary schools were recruited and all Year 7 girls who were physically able to participate in Physical Education (PE) classes were invited to participate. For practical reasons the sample was limited to 30 girls per school. Three intervention schools received two 90-minute after-school dance classes per week, for nine weeks. Following extensive formative work [12,14-16], the sessions were based on hip-hop and street dance genres. All participants were asked to wear an Actigraph accelerometer for seven days at baseline (Week 0), during the last two weeks of the intervention (Week 8 or 9) and 3 months after the intervention ended (Week 20). The feasibility trial demonstrated that it is possible to recruit Year 7 girls and record the cost of the programme. An embryonic resource-use checklist was developed for use in the main trial economic evaluation. We also showed that girls would attend the dance sessions and it was feasible to collect PA data from the girls at three time points. The feasibility work suggested that it would be possible to achieve a mean increase of 10 additional minutes of MVPA per weekday (i.e. 50 minutes per week) if the session intensity was increased and inactive creative time reduced.

Evidence of cost-effectiveness is important for knowing where to invest scarce resources and commission programmes to maximise health outcomes in the population [17,18]. However, gathering the evidence is a challenge [19] where behaviour change is associated with health outcomes that have wider cultural and environmental determinants [20,21]. The feasibility trial demonstrated that it was possible to cost the dance programme, but the cost-effectiveness was not ascertained.

### Aims of the current study

The current study builds on the feasibility trial by examining the effect of a dance intervention on the MVPA levels of Year 7 girls. The specific research aims of the BGDP trial are as follows:

#### **
*Primary aim*
**

1. Determine the effectiveness of the BGDP intervention to improve the objectively-assessed (accelerometer) mean weekday minutes of MVPA accumulated by Year 7 girls one year after the baseline measurement (T2 = time 0 + 52 weeks).

#### **
*Secondary aims*
**

2. Determine the effectiveness of the BGDP intervention to improve the following secondary outcomes among Year 7 girls at T2:

a) Mean weekend day minutes of MVPA;

a) Mean weekday accelerometer counts per minute (providing an objective measure of the volume of overall PA in which participants engage);

a) Mean weekend day accelerometer counts per minute;

a) The proportion of girls meeting the recommendation of 60 minutes of MVPA per day;

a) Mean accelerometer-derived minutes of weekday sedentary time;

a) Mean EQ-5D-Y scores (EuroQol 5D Youth survey - a standardised instrument for measuring health outcomes);

a) Programme costs (school level).

3. Determine the effectiveness of the BGDP intervention during the intervention period (weeks 19–20 of the intervention – first follow-up) on all primary and secondary outcome variables.

4. Determine the extent to which any effects on primary and secondary outcomes are mediated by autonomous and controlled motivation towards PA and perceptions of autonomy, competence and relatedness in PA [8].

5. Determine the cost-effectiveness/utility of the intervention from a public sector perspective over the time frame of the study.

## Design

BGDP is a two-armed cluster randomised control trial in 18 secondary schools. The trial includes process, economic, quantitative and qualitative evaluations. The 18 schools will be recruited from state secondary schools (excluding Special Educational Needs, dance academies and privately/independently funded schools) operating within three Local Authorities: Bristol City Council, North Somerset Council, and Bath and North East Somerset Council. We aim to recruit up to 33 Year 7 girls from each school, with a minimum of 25 participants in each (450–594 participants overall). Schools must have at least 30 Year 7 girls, and be able and willing to allocate space for two after-school sessions per week for 20 weeks.

All schools fulfilling the inclusion criteria will be invited to participate and the first 18 schools that agree to participate will be enrolled. Additional schools will be placed in a reserve pool. If fewer than 25 girls are recruited in a given school, we will recruit a different school. Nine schools will be randomly assigned to the intervention arm and nine to the control arm.

### Participant recruitment

Following school recruitment, a participant recruitment campaign will be initiated in all 18 schools. A taster session will be provided for all Year 7 girls who are able to engage in PE classes. The sessions will be delivered by an external dance instructor. At the end of the taster session students will be told about the study (including details of the randomisation and data collection commitments). All girls will be provided with information packs for themselves and their parents, and will be asked to return informed consent forms. If more than 33 consent forms are returned in each school, 33 girls will be randomly selected to participate using a computer-generated algorithm. If a girl drops out of the study prior to baseline data collection she will be replaced by the first randomly chosen reserve, with this process repeated as necessary. No replacements will be made after baseline collection. All participants will receive a £10 gift voucher on completion (return of accelerometer) of each of the data collection phases (£30 in total). The study has been granted ethical approval from the funder, sponsor and the School for Policy Studies ethics committee at the University of Bristol. Written informed parental consent will be obtained for all participants.

### Sample size

Sample size calculations were performed to detect a mean difference of ten minutes of weekday MVPA between the intervention and control groups. The un-inflated sample size required for analysis to detect a difference of 10 minutes/day MVPA - assuming a standard deviation of 18 minutes [14] with 90% power and 5% two-sided alpha is 68 per arm. We estimated the 95% Confidence Interval (CI) for the school-associated Intra-class Correlation (ICC) in the pilot study to be < 0.001 to 0.087. If we assume that 20% of participants will not provide primary outcome data, the mean cluster size for analysis will be 24, resulting in a design effect of 3.0 using the upper 95% confidence limit for ICC. Thus, we will recruit a total of 18 schools and at least 450 girls.

### Randomisation

Randomisation will occur at the school level after baseline data has been collected. Balance between trial arms will be achieved with respect to Local Authority membership, mean minutes of participant MVPA at baseline, school size, and deprivation. Deprivation will be assessed as the percentage of pupils in the school eligible for the Department of Education’s Pupil Premium (additional funding given to schools to support disadvantaged pupils and bridge the attainment gap between them and their peers).

### Intervention description

Schools randomised to the intervention arm will receive a 20-week dance intervention, consisting of 2 × 75 minute after-school sessions per week (40 sessions in total), running between January and June 2014. Dance sessions will be led by an external dance instructor who will deliver a standardised programme which was developed in the feasibility trial. Instructors will attend a training programme before the intervention begins and a 'booster session’ after the first term of delivery. The dance programme focuses on building participants’ perceived autonomy to be active and perceived dance competence in a social, autonomy-supportive environment. The programme provides exposure to a wide range of dance styles. Participants in intervention schools will each be given a 'dance diary’ which they will be encouraged to complete between sessions. The diaries will help children to reflect on their learning and encourage them to set their own goals.

### Control school provision

Schools in the control arm will not receive the dance intervention and will continue with their normal schedule. Control schools will receive a £500 donation to the general school fund once all data has been collected from participants.

### Measures

Data will be collected from all participants (intervention and control) at three time-points.

1. Time 0 (T0) (baseline), September-November 2013.

2. Time 1 (T1) (baseline +19-20 weeks), June 2014.

3. Time 2 (T2) (baseline + 52 weeks), September-November 2014.

The following measures will be measured at each time point: 1) accelerometer-assessed PA; 2) self-completed psychosocial questionnaire containing variables that we hypothesise to function as mediators (including self-esteem measures); 3) self-completion of the EQ-5D-Y health questionnaire, and; 4) height and weight. Details of each measurement are outlined below. In addition at T0, for descriptive purposes, all parents will be asked to report their home postcode; which will be used to estimate the index of multiple deprivation for the primary residence. Girls will also be asked to self-report their level of dance experience using categories of 'none’, 'some’ or 'a lot’.

### Accelerometer assessed PA

Participants will wear an Actigraph GT3X+ accelerometer for seven days. Periods of ≥60 minutes of zero values will be defined as accelerometer’non-wear’ time and discarded. Participants will be included in the analysis if they provide ≥3 days (weekday or weekend) of data with at least 500 minutes of data between 06:00 and 23:00.

Mean minutes of daily MVPA will be established using the threshold developed by Evenson et al. [22], which has been shown to be an accurate threshold for this age group [23]. The following accelerometer variables will be derived:

#### **
*Primary outcome*
**

1. Mean MVPA on weekdays a year after baseline measurement (T2).

#### **
*Secondary outcomes*
**

2. Mean weekend day minutes of MVPA (T1 and T2);

3. Mean weekday minutes of MVPA (T1 and T2);

4. Mean weekday accelerometer counts per minute (providing an indication of the volume of activity in which the girls engage) (T1 and T2);

5. Mean weekend day accelerometer counts per minute (T1 and T2);

6. Proportion of girls meeting the recommendation of 60 minutes of MVPA per day (T1 and T2);

7. Mean minutes of sedentary time per weekday (≤100 counts per minute) (T1 and T2).

### Psychosocial questionnaire

All participants will be asked to complete a 66 item questionnaire at each time point. The questionnaire, which will be programmed onto a tablet computer, will assess psychosocial variables that could be influenced by the intervention and/or mediate the effect of the intervention on MVPA. Aligned with SDT, autonomous (8 items) and controlled motivation (7 items) [24] and perceptions of autonomy (6 items), competence (6 items) and relatedness (5 items) [25,26] within PA will be measured. Self-esteem (9 items) [27] will also be measured. All measures were piloted in the feasibility trial [14] and displayed evidence of internal consistency among Year 7 girls. Following reverse scoring of negatively worded items, subscale mean scores will be calculated.

As shown in Figure 1, we hypothesise that autonomous and controlled motivation for PA, and perceptions of autonomy, competence and relatedness in PA will mediate the effect of the intervention on weekday MVPA.

**Figure 1 F1:**
[figure not shown]
Hypothesised mediation model.

### Costs/economic outcome data

The EuroQol 5D Youth survey (EQ-5D-Y), validated for use in children and adolescents [28], will be applied as a secondary outcome measure of health related quality of life in the trial. The EQ-5D-Y questionnaire is a standardised instrument for measuring health outcomes in youth. Public sector resources used at each stage of programme delivery will be recorded retrospectively using the resource use checklist tool developed during the feasibility study. Time sheet, expenses and travel data records will all be utilised. Costs will be estimated using the checklist tool developed for this purpose and prices from published or established sources. Costs will be uprated in line with inflation to 2014–15 prices.

### Process evaluation

A process evaluation will be conducted in the nine intervention schools. The process evaluation will report on consent, recruitment, attendance and adherence rates. The dose of the intervention (i.e. number of planned sessions delivered) will be recorded for each school. Intervention fidelity will be assessed by: a) dance instructors’ completion of a log-book indicating whether they delivered planned core components of each session (*fully*, *partially* or *not at all*); and b) observation/audio recording of four random sessions delivered by each dance instructor. Observers will rate the degree to which the instructors delivered the core components of the session. Audio recordings will be rated using a validated tool [29], to measure the extent to which dance teachers’ teaching style was autonomy-supportive. At the end of the four observed sessions in each school, participants will be asked to complete a perceived exertion [30] and enjoyment [31] questionnaire.

To assess any contamination of the control group from dance classes locally, we will collect data on extra-curricular provision (including dance) in all 18 schools. School-level data will be collected from school staff at each measurement point. Additionally, girls will be asked if they attend dance classes outside of school at each measurement point. Any girls who withdraw from the intervention will be asked to complete an exit questionnaire to explore their reasons for withdrawal.

### Statistical analysis

The analysis and presentation of the trial will be in accordance with CONSORT guidelines, with the primary comparative analyses being conducted on an intention-to-treat (ITT) basis and due emphasis placed on confidence intervals for the between-arm comparisons. To take appropriate account of the hierarchical nature of the data, we will use multivariable mixed effects linear regression to estimate difference in the primary outcome for intervention group versus control, adjusting for baseline MVPA and randomisation variables. In a secondary analysis, we will further adjust for variables that were imbalanced between the trial arms at baseline. To assess the potential effect of missing data on the outcomes, in sensitivity analyses we will impute data using standard multiple imputation approaches.

We will investigate the effect of adherence to the intervention using instrumental variable regression, with adherence defined as girls attending 25 of the 40 sessions. Appropriate interaction terms will be entered into the primary regression analyses for mean weekday MVPA in order to conduct pre-specified subgroup analyses that will include baseline level of dance experience ('none’, 'some’ or 'a lot’), socioeconomic position (based on the index of multiple deprivation for the home postcode – continuous variable), and baseline weekday minutes of MVPA (continuous variable). Since the trial is powered to detect overall differences between the groups rather than interactions of this kind, these analyses are considered exploratory and results will be presented using confidence intervals and interpreted with due caution.

We will explore whether the effect of the intervention on the primary and secondary outcomes is mediated by autonomous and controlled motivation for PA and/or perceptions of autonomy, competence and relatedness need satisfaction in PA. This will be achieved by methods based on the processes of Emsley and colleagues [32].

Quantitative process evaluation data (e.g. attendance rates) will be analysed using appropriate descriptive statistics for normally distributed variables (using the mean and standard deviation) and variables without such a distribution (using the median and inter-quartile ranges). Ratings of instructor's teaching styles will be made from audio recordings combined with real time observation notes. Each item will be rated in every 5 minute lesson period, these values will be summed and divided by the number of five-minute intervals in the lesson. Item scores will be summed to provide quantitative scores for five teaching elements; Relatedness support, Structure before the activity, Structure during the activity, autonomy support and controlling teaching behaviour.

### Economic analyses

Economic analysis will be set within a cost 'effectiveness’ framework. The mean incremental costs associated with intervention delivery at the school level will be estimated from a public sector perspective [14]. Public sector costs will be related to incremental change in accelerometer-derived MVPA minutes per weekday and incremental change in EQ-5D-Y scores to estimate cost per minute of MVPA, cost per Quality-adjusted Life Year (QALY), average cost per school and average cost per user, with the associated CIs reported. EQ-5D-Y will be administered at T0, T1 and T2. We will also extend the balance sheet framework to include the proportion of participants meeting the 60-minute per day MVPA recommendation. Programme costs will also be determined at the school level.

Confidence intervals for the *incremental cost-effectiveness ratio* (ICER) will be calculated using bootstrapping at the school level. If appropriate we will produce cost-effectiveness acceptability curves for a range of thresholds and conduct threshold analysis to compare our cost per QALY estimates with National Institute for Health and Care Excellence (NICE) benchmark values. The time frame for the health economic evaluation is the length of the study, as the focus is to consolidate learning from our feasibility study in a full trial, and not to attempt to make long term predictions of cost-effectiveness at this stage. Uncertainty will be explored using sensitivity analyses and findings will be presented for a range of decision makers at the societal and funder levels, including Local Authorities and the National Health Service (NHS), from a public sector perspective.

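### The only uncertainty measure promised without condition for cost-effectiveness is an ICER interval, which cannot be read if the bootstrap effect crosses zero; the curve that would still work is optional

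*Protocol article*

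**What the plan says.** In the protocol article, Economic analyses, public sector costs are set against incremental change in weekday MVPA and in EQ-5D-Y score "to estimate cost per minute of MVPA, cost per Quality-adjusted Life Year (QALY), average cost per school and average cost per user", and confidence intervals are promised for these quantities. Those for the ICER "will be calculated using bootstrapping at the school level". The next sentence reads: "If appropriate we will produce cost-effectiveness acceptability curves for a range of thresholds", followed by a threshold analysis against NICE benchmark values. What would make the curves appropriate is not stated. The section adds that "Uncertainty will be explored using sensitivity analyses". It mentions neither net monetary benefit nor a cost-effectiveness plane, and gives no rule for bootstrap replicates in which the incremental effect is zero or negative.

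Two other places bear on the point. Control school provision says that control schools do not receive the dance programme. The Design part of the abstract places the primary time point six months after the intervention ends and names cost-effectiveness within the primary interest, although Aims of the current study lists it as the fifth aim, under the secondary aims.

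**The concern.** An ICER divides incremental cost by incremental effect. With a positive numerator, a small positive effect gives a very large positive ratio and a small negative effect gives a very large negative one. Negative ratios here come from replicates in which the programme costs more and does worse, yet on the number line they lie below every favourable value. Once an appreciable share of replicates falls on the wrong side of zero, the limits of a ratio interval no longer order outcomes from better to worse value.

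The plan promises this interval whatever the result. The acceptability curve, which does not break at zero effect, depends on a judgement left open. If the effect is small, Local Authorities and the NHS, which the plan names as audiences, could be given an interval with no usable reading, and whether to add the curve would be decided after the result is known.

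**Working it through.** **Reproducing the plan's own figures.** Sample size section: the trial is sized "to detect a mean difference of ten minutes of weekday MVPA between the intervention and control groups", and the un-inflated number "assuming a standard deviation of 18 minutes [14] with 90% power and 5% two-sided alpha is 68 per arm".

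- n per arm = 2 × [18 × (1.96 + 1.2816) / 10]² = 68.09, which agrees with 68.
- The ICC interval is given as "in the pilot study to be < 0.001 to 0.087". With 24 girls analysed per school, the design effect at the upper limit is 1 + 23 × 0.087 = 3.00, as stated.
- Schools needed = 2 × 68 × 3.00 / 24 = 17.0, so 18 is enough.

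**Standard error of the MVPA difference.** With 9 schools of 24 girls per arm, SE = 18 × √(2 × DE / 216), where DE = 1 + 23 × ICC.

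- ICC 0.001: DE 1.023, SE 1.75 min.
- ICC 0.03 (an assumed middle value): DE 1.69, SE 2.25 min.
- ICC 0.087: DE 3.00, SE 3.00 min.

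These use the unadjusted SD of 18.

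**How often the effect distribution crosses zero.** Take crossing to mean that more than 2.5% of replicates have an effect of zero or less, that is, that the 95% CI for the effect reaches zero or below. For true effect δ the normal approximation is Φ(1.96 − δ/SE).

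| True T2 effect | ICC 0.001 | ICC 0.03 | ICC 0.087 |
|---|---|---|---|
| 10 min (planned) | 0.0% | 0.7% | 8.5% |
| 5 min (assumed) | 18.6% | 39.7% | 61.5% |
| 3 min (assumed) | 59.8% | 73.5% | 83.2% |
| 0 min (assumed) | 97.5% | 97.5% | 97.5% |

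Worked example: δ = 10 and SE = 3.00 give Φ(1.96 − 3.33) = Φ(−1.37) = 0.085. A simulation that resampled 9 schools per arm gave somewhat lower figures: 0 to 7.2% at 10 min, 16.9 to 54.5% at 5 min and 54.2 to 76.8% at 3 min, over ICC 0.001 to 0.087.

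**What the interval looks like.** Assume an incremental cost of 100 (SE 7, arbitrary units) and an effect SE of 3.0 min, and take simple percentile limits as an illustration.

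- Estimated effect 10 min: 6.1 to 24.3 per minute, with 0.05% of replicates negative. This is readable.
- Estimated effect 2 min: −424 to 435 per minute, with 25% of replicates negative (Φ(−2/3.0) = 0.25). This is not readable. It contains ratios near zero, which would need a very large effect in one direction or the other, and it excludes the very large positive ratios that a small gain produces.

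**The same case as net benefit.** Value a minute at 50, which is the point ICER, 100/2. Net benefit is 50 × 2 − 100 = 0. Treating cost and effect as independent, its SE is √[(50 × 3.0)² + 7²] = 150.2, so the 95% CI is 0 ± 1.96 × 150.2, or −294 to 294. The limits run from worse to better value, with no break at zero effect.

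**QALYs.** The document gives neither an expected EQ-5D-Y difference nor its SD, so no corresponding probability can be calculated.

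**The case against.** The strongest reply is that the plan was sized for a 10-minute gain, and there the interval behaves well. The chance of an estimate at or below zero is at most Φ(−10/3.0) = 0.0004, and crossing in the sense used here occurs in at most 8.5% of trials. The 3.0-minute SE is the unfavourable end of the ICC range, and the planned adjustment for baseline MVPA would normally reduce it. Acceptability curves, a threshold analysis and sensitivity analyses are already mentioned, and the between-arm effect and its CI will be reported prominently, so a failed programme would hardly be hidden. Bootstrap detail may also sit in a full analysis plan that is not shown.

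Much of this stands, and it rules out several stronger readings.

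- A reader might infer that an ICER interval never has a valid meaning. It does when nearly all replicates show a positive effect.
- A reader might infer that a null or negative effect is likely in this trial. No figure in the document says so. The T2 timing, and the feasibility work's conditioning of the 10 minutes on changed sessions, make a smaller effect plausible and no more.
- A reader might infer that the plan uses an uncorrected percentile bootstrap that ranks harmful replicates as the cheapest, or that understates variance with nine schools per arm. The plan names neither the percentile method nor an uncorrected one.
- A reader might infer that the interval fails to cover the true ratio. In the simulation, percentile limits covered it in about 90 to 96% of trials, so the fault lies in how the interval can be read.

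What the reply does not remove is the order of commitment. The article itself fixes the fragile measure for every result and leaves the sound one to an unstated judgement. Sensitivity analyses do not make an unreadable interval readable.

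**Conclusion.** The point holds in limited form. The one uncertainty measure promised unconditionally for cost per MVPA minute and cost per QALY cannot be interpreted when the bootstrap effect distribution crosses zero, and the planned measure that survives this is conditional. For MVPA the risk is at most about 8.5% at the planned effect, about 19 to 62% at 5 minutes and about 60 to 83% at 3 minutes. For QALYs it is plausible but not quantifiable.

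This rests on a positive incremental cost, which is reasonable because only intervention schools receive the programme; on SD 18 without baseline adjustment; on 24 analysed girls in each of 18 schools; on ICCs from 0.001 to 0.087; and on a normal approximation. The 5 and 3 minute effects are assumptions. The change is worth making because the summary should work for whatever result arrives. The point does not question resampling by school or the sample size.

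**What to change.** Keep the school-level bootstrap and change how its replicates are summarised.

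1. Make incremental net monetary benefit, with its CI, the main expression of uncertainty: at stated willingness-to-pay values for QALYs, and over a stated range of values per MVPA minute.
2. Remove the opening condition from the sentence on acceptability curves, so that the curve and the cost-effectiveness plane are produced in every case.
3. Report the ICER as a point estimate, with an interval only when the CI for the incremental effect excludes zero.

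No new data or resampling is needed. The real cost is that a range of values per MVPA minute must be chosen and stated in advance; for QALYs, the NICE benchmarks that the plan already cites can serve.
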